## Abstract

**Background:**

Chronic neck pain (CNP) is a common and disabling musculoskeletal disorder in developing and developed countries. Previous studies have shown that *tuina* and traditional Chinese massage are effective treatments for patients with CNP. However, there is little evidence to support the use of one intervention over the other. The aim of this study is to compare the effects of *tuina* and traditional Chinese massage in the treatment of pain and disability in patients with CNP.

**Methods/design:**

This is a multicenter, assessor- and analyst-blinded, randomized controlled trial with two parallel arms: a *tuina* group and a traditional Chinese massage group. A total of 356 eligible CNP patients will be randomly assigned to the groups in a 1:1 ratio. The intervention in the *tuina* group includes both structural and relaxation massage, while the traditional Chinese massage group will receive relaxation massage only. The interventions for both groups will last for 15 min and will be carried out three times a week for a period of 4 weeks. The primary outcome will be changes in the Northwick Park Neck Pain Questionnaire. Secondary outcomes will be measured by a visual analogue scale (VAS), the Neck Disability Index (NDI), and the 36-item Short-Form Health Survey (SF-36). The data will be analyzed at the baseline, at the end of the intervention, and during the 3 months of follow-up by repeated measures analysis of variance. The significance level is 5%. The safety of *tuina* and traditional Chinese massage will be evaluated after each treatment session. The results of this trial will help clarify the value of *tuina* and traditional Chinese massage as treatments for CNP and will highlight any differences in the efficacy of the treatments.

**Discussion:**

The purpose of this trial is to determine whether *tuina* is more effective than traditional Chinese massage in adults with CNP. This trial will, therefore, contribute to providing a solid foundation for clinical treatment of CNP, as well as future research in massage therapy.

**Trial registration:**

Chinese Clinical Trial Registry, ChiCTR-INR-17013763. Registered 8 December 2017.

**Electronic supplementary material:**

The online version of this article (10.1186/s13063-018-3096-3) contains supplementary material, which is available to authorized users.

## Background

Chronic neck pain (CNP) is a serious public health and socioeconomic problem worldwide. Studies have shown that the overall prevalence of CNP varies from 0.4% to 86.8% (mean 23.1%), while the 1-year incidence of CNP in a high-risk population (office and computer workers) ranged from 10.4% to 21.3%, which is greater than for manual workers [1]. CNP is characterized by activity limitations, pain, dizziness, anxiety, and insomnia [2]. A cross-sectional study showed that health-related quality of life was also negatively correlated with prevalent neck pain [3], and the existence of neck pain was also a predictor of poor future physical health-related quality of life in a longitudinal study [4]. Moreover, CNP causes a significant socioeconomic impact, not only due to direct medical costs, but also due to indirect health-care costs and loss of productive capacity [5, 6].

The pathophysiology of CNP is not well established due to difficulties in localizing the source of the pain. Potential causes of CNP include, but are not limited to, changes in the spinal disc structure with aging and degeneration, as well as changes in local concentrations of cytokines such as matrix metalloproteinase, phospholipase A2, nitric oxide, IL-1β, IL-6, C-reactive protein, and tumor necrosis factor α (TNF-α) [7]. Specific conditions contributing to CNP include degeneration, inflammation, infective and neoplastic causes, metabolic bone diseases, referred pain, psychogenic pain, trauma, congenital disorders, exposure to tobacco from direct smoking, physical activity, and repetitive and sedentary work positions [8].

Depending on the tailored treatment strategies, various treatment modalities are available for CNP including medication (non-steroidal anti-inflammatory drugs and serotonin reuptake inhibitors) and interdisciplinary rehabilitation, physical therapy, spinal injections, and surgical interventions [9–11]. Although pain-relieving medication is most frequently used to alleviate CNP, long-term use of non-steroidal anti-inflammatory drugs is limited due to the risk of side effects and patient intolerance [9]. Complementary therapies such as massage, acupuncture, neck exercises, mechanical traction, herbal medicine, cupping, electrotherapy, and exercise are well accepted as alternative treatments for CNP due to their positive effects and safety profile [12–14]. There have been many trials on the use of traditional Chinese massage to treat CNP. However, there is considerable controversy regarding its efficacy due to poor treatment precision, variations in treatment, inadequate sample sizes, low methodological quality, and subclinical dosing regimens of trials to date.

*Tuina* is commonly defined as an ancient healing art using fingers and strength [15]. In treating CNP with *tuina*, the spinal joints are adjusted with the lightest strength for as short as possible to obtain the best clinical curative effect. In recent years, its efficacy has been confirmed by many trials [12, 14]. Thus, we designed a randomized controlled trial (RCT) to investigate whether *tuina* is more effective than traditional Chinese massage in treating CNP. This trial will, therefore, contribute to providing solid clinical evidence on the efficiency of *tuina* and traditional Chinese massage for CNP, as well as future research in massage therapy.

## Methods/design

### Study design

This is a multicenter, assessor- and analyst-blinded RCT with two parallel arms: a *tuina* group and a traditional Chinese massage group. The study protocol has been approved by the Regional Ethics Review Committee of Yueyang Hospital of Integrated Traditional Chinese and Western Medicine affiliated with Shanghai University of Traditional Chinese Medicine (project number: 2017–028). It has been registered in the Chinese Clinical Trial Registry (ChiCTR-INR-17013763). A total of 352 eligible CNP patients will be randomly assigned to the groups in a 1:1 ratio. Written informed consent will be provided by all patients. Outcome assessment and statistical analyses will be performed by independent researchers who are blinded to patient assignment. The study design is illustrated in the flow chart in Fig. 1 and the study schedule is presented in Fig. 2.

**Fig. 1 Fig1:**
[figure not shown]
Flow chart of the study. A total of 356 participants will be randomized to the two groups. The interventions will last for 15 min and will be carried out three times a week for 4 weeks. The study period will be consisted of the baseline, 2 weeks of treatment, after treatment, 1.5 and 3-month follow-up. NDI Neck Disability Index, NPQ Northwick Park Neck Pain Questionnaire, SF-36 36-item Short-Form Health Survey

**Fig. 2 Fig2:**
[figure not shown]
Study schedule showing time points for enrollment and assessment. NDI Neck Disability Index, NPQ Northwick Park Neck Pain Questionnaire, SF-36 36-item Short-Form Health Survey, VAS visual analogue scale, W-1 screening before enrollment, W0 baseline assessment, W2 assessment after the sixth treatment, which is in the second week, W4 assessment after the 12th treatment, which is in the fourth week, W10 assessment 10 weeks after the first treatment, W16 assessment 16 weeks after the first treatment

The main treatment center will be Yueyang Hospital of Integrated Traditional Chinese and Western Medicine affiliated with Shanghai University of Traditional Chinese Medicine, which will enroll 116 participants. Three other treatments centers—Sixth Hospital of Shanghai, Shuguang Hospital affiliated with Shanghai University of Traditional Chinese Medicine, and Jiading District Hospital of Traditional Chinese Medicine—will each enroll 80 participants.

### Participants and recruitment

Eligible participants are patients diagnosed with CNP according to the clinical guideline for traditional Chinese medicine (Criteria of Diagnosis and Therapeutic Effect of Diseases and Syndromes in Traditional Chinese Medicine, ZY/T001.1–94). Patients whose neck pain has persisted without relief for over 2 weeks such that it impairs their daily activities at work or elsewhere will be informed of this trial. If a patient expresses interest, a clinical trial communicator will describe the trial to them and ask whether they would like to join it. If the answer is yes, a face-to-face interview will be conducted in the reception room for clinical research subjects in the four hospitals. Patients who meet the inclusion criteria and do not meet the exclusion criteria can join once they sign the consent form.

We publicized the trial to potential participants in four ways: 1) by approaching patients with neck pain admitted to an outpatient department or inpatient ward in each center, 2) recruitment posters at each center and nearby community centers, 3) the official microblog and WeChat platforms of each center, and 4) printed adverts in newspapers.

### Inclusion criteria

Participants who meet all the following criteria can be enrolled:With neck pain as their main symptom for at least 3 months but less than 2 yearsEpisodes of pain lasting for over 30 min, and frequency of pain occurring at least once per monthPain intensity of more than 3 points as measured on a visual analog scale (VAS) at the time of recruitmentNo massage or other relevant treatment has been received within the 7 days prior to study entryAged 20–60 years, male or femaleAble and willing to comply with the intervention and follow-up evaluationAgree not to receive other relevant treatments during the period of treatment (including muscle relaxants)Able to provide written informed consent

### Exclusion criteria

Participants meeting any of the following criteria will be excluded:History of cervical intervertebral disc herniation accompanied by nerve symptoms; neck trauma; surgical neck fracture; spinal disease; infectious inflammatory autoimmune diseases; congenital vertebral anomalies; or compression fracturesWith a severe primary disease such as cardiovascular, cerebrovascular, liver, or kidney diseaseUnable to communicate or provide self-care due to a psychiatric or psychological disorder related to severe neurosis or due to dementiaWomen who are pregnant or lactatingPartial injury in acute phase or with local skin damageDuration of neck pain or neck stiffness episodes of less than 0.5 hPain episodes have occurred for less than 3 months or more than 2 yearsFailure to adhere to the treatment at the prescribed timeUse of massage or other relevant treatment within 7 days prior to study entryParticipating in other clinical trialsUse of any other treatment (drug or non-drug)

### Dropout criteria

Participants who do not complete the clinical protocol for the following reasons should be considered as dropped out:The patient quits (poor efficacy or adverse reactions)Loss to follow-upResearchers remove the patient (poor compliance, complications, or serious adverse events)

The trial communicator will communicate in-depth with patients who want to withdraw from the trial because of poor efficacy or have no time to promote retention.

### Comprehensive suspension criteria

The trial will be suspended if:The investigators discover a significant safety problemThe therapeutic effect is poor (We will asses the therapatic effect at week2)There is a major mistake in the planThe sponsor has a huge problem in funding or management

### Randomization

In this trial, the Department of Science and Technology of Yueyang Hospital will generate the randomization sequence using a random number generator (SPSS 21.0, SPSS Inc., Chicago, IL, USA). Random numbers will be placed in opaque envelopes, numbered sequentially, and sent to a therapist. The envelopes are opened in numerical order to determine the allocation for participants who pass the screening test. The unmasking is performed by the therapist after the baseline questionnaire is filled in, after the physical examination, and after checking the exclusion criteria, so that the study administrator, the therapist, and the study participant are blinded to the group assignment until after all baseline data have been collected.

### Blinding

Patients will not be informed of the type of treatment that they will receive. Outcome assessors, data managers, and the statistician will be blinded in this trial and do not share study information with each other. To preserve masking, only the massage therapists will have access to treatment allocation. However, they must learn how to use the blinding method to communicate with participants to ensure treatment blinding. The blinding procedure will be operated until the data are locked.

### Interventions

Participants will receive 12 sessions of treatment over a period of 4 weeks. Treatment will be performed by a senior therapist who has studied acupuncture and massage and has held a practitioner’s license for more than 10 years. They must have received professional training in *tuina* and massage. They must pass a test to ensure consistency of study methods before participating in the trial. The participants will be asked to rest for 15 min before treatment. A constant room temperature of 23 to 25 °C will be maintained to ensure the patients are comfortable and relaxed during treatment. Subjects will be advised to lie in the prone position on the treatment couch. The interventions will be performed three times a week. Each session will last for 15 min. Neck function will be assessed at baseline as well as at 2, 4, 10, and 16 weeks after the baseline assessment.

### *Tuina* group

In this arm of the study, the therapist will administer a two-step protocol intended to ease neck pain and improve neck functional activity disorders by releasing the soft tissue of the neck and shoulders, by inducing a state of general relaxation while addressing specific structural issues determined by the clinician to be likely to contribute to the patient’s CNP, or by promoting *qi* movement (which according to traditional Chinese medicine theory activates blood circulation). The specific protocol used is described below.

#### Step one: local manipulation

Patients are instructed by the therapist to lie in the lateral position and to relax their mind and body naturally. Neck pain conditions can be carefully examined prior to treatment. Tender tissue, trigger points, contracted muscle tissue (knots), and nodules are identified for further treatment. The therapist first relaxes the soft tissue from the neck and shoulders to the upper back for 5 minutes. The pain point is the *a-shi* point in acupuncture theory. It is generally recognized as reflecting the underlying condition and is frequently manipulated to stop pain. The pain point is pressed in the neck region in a direction perpendicular to the erector spine for 5 min. This step will be performed to resolve adhesions and to increase general circulation with muscle pressing, stripping, and deep tissue kneading manipulation. The manipulation will be gradually intensified and enlarged. It is intended to unblock *qi* stagnation, remove blood stasis by separating adherent fascicles, and resolve contracted muscle nodules. The amount of force used is determined by the patient’s *deqi* sensation, which is often described as a dull pain, heaviness, numbness, or soreness, and commonly regarded as an indicator of manipulation efficacy in acupuncture and *tuina* [16–18].

#### Step two: neck structural rectification

Neck structural rectification is performed after the above procedures have relieved the tension in muscles and soft tissues. The patient will be instructed to lie in the lateral position with the affected side up. The therapist presses one thumb on the anterior intercondylar nodule of the lordotic segment of the lesion while the palm of the same hand holds the lower jaw. The other thumb is pressed on the upper or lower vertebral articular while the palm holds the occipital. The operator first stretches the patient’s neck longitudinally for a moment, then corrects the sagittal shift of the cervical spine by adjusting the diseased segment lightly with both thumbs. At the end of the treatment, the therapist relaxes the patient’s neck by gentle traction and twisting forces with both hands. All manipulations will last 5 min.

### Traditional Chinese massage group

The traditional Chinese massage group will receive relaxation therapy for neck pain. The protocol has two steps.

#### Step one: click on the acupuncture point manipulation

The therapist instructs the patient to sit, and then presses and kneads GB20, GB21, SI14, LI15, LI11, and LI4 for 1 min each.

#### Step two: local manipulation

The therapist applies a roll and *nafa* (characterized by a pinch and lift up) to relax the muscle and soft tissue of the neck and shoulders. This procedure will last for 9 min.

### Allowance of concurrent treatment of patients

All treatments for CNP are banned during the trial, including oral muscle relaxants, narcotics, analgesics, surgery, drug injections, acupuncture, and physical therapy. They may receive any treatment that is not related to neck pain. Any change in concurrent treatment will be recorded at every visit.

### Outcome measurements

Four well-recognized self-report tools will be used to measure the outcomes. The Northwick Park Neck Pain Questionnaire (NPQ) will be used as the primary outcome measure. A VAS, Neck Disability Index (NDI), and Short Form 36 (SF-36) will be used as secondary outcome measures. Neck pain-related dysfunction, pain, and quality of life will be assessed at six time points: screening, baseline (after enrollment), weeks 2 (intervention session), 4 (intervention session), 10 (follow-up session), and 16 (follow-up session). We will measure the study participant’s previous experience of the interventions, their expectations for recovery, and their expectation of the importance of the allocated therapy in their recovery (just after the unmasking and before the intervention starts).

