Data normality will be tested through visual inspection of histograms. According to the results of the homogeneity and normality analysis, parametric statistics (Tukey test) or non-parametric statistics (Wilcoxon rank sum test) will be used for the within- and between-group analyses. Descriptive statistics will be used to compare demographic and baseline information and to evaluate the credibility of the groups. If an adjustment for possible baseline incomparability is needed, a covariance analysis will be performed. Efficacy is measured at five time points. Therefore, a repeated measures analysis of variance will be used to investigate the effect of treatment, time, and interaction terms between treatment groups versus time. Two-sided paired *t* tests will use within-group comparisons (comparing baseline to follow-up). A chi-squared test or a Fisher’s exact test will be performed to determine categorical variables between groups and adverse effects, which will be recorded and described as a frequency and percentage. Fisher’s exact test will be used if a cell has an expected value of less than 5 that is equal to or more than 20%. All statistical analyses will be performed with the Statistical Package for Social Sciences (SPSS, version 21.0, SPSS Inc., Chicago, IL, USA) by statisticians who are independent of the research team and blinded to the group allocation. The confidence interval will be established at 95%, and the significance level at 0.05.

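### Screening is counted as an outcome assessment in one section but not in three others, so any screening scores enter no described analysis, and baseline adjustment is only conditional

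*Protocol article*

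**What the plan says.** The protocol article gives two counts of outcome assessments.

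- **Six.** Outcome measurements: "assessed at six time points: screening, baseline (after enrollment"), then weeks 2 and 4 during the intervention and weeks 10 and 16 in follow-up.
- **Five.** Interventions: "Neck function will be assessed at baseline as well as at 2, 4, 10, and 16 weeks after the baseline assessment". The Fig. 1 caption: "The study period will be consisted of the baseline, 2 weeks of treatment, after treatment, 1.5 and 3-month follow-up". Statistical analyses: "Efficacy is measured at five time points".

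The Fig. 2 caption lists "W-1 screening before enrollment, W0 baseline assessment" as separate entries, so the count of six does not come from naming one visit twice. The grid showing which scale is taken at which visit is in the figure itself, which is not available here.

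For the analysis, Statistical analyses says that "a repeated measures analysis of variance will be used to investigate the effect of treatment, time, and interaction terms between treatment groups versus time". Baseline enters as a covariate only under a condition: "If an adjustment for possible baseline incomparability is needed, a covariance analysis will be performed".

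Primary outcome measurement counts a patient as a success when NPQ improvement exceeds 30%. It does not name the score from which improvement is measured.

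**The concern.** Either Outcome measurements is wrong and not every scale is scored at screening, or a set of pre-treatment scores is collected that no described analysis uses. Both readings call for a correction to the text.

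If the scores exist, they are usable. The Randomization section keeps allocation masked until all baseline data are in, so W-1 and W0 both precede unmasking and either is a valid covariate. Two pre-treatment scores predict a fluctuating outcome somewhat better than one.

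The conditional covariance analysis matters for the same reason. If adjustment depends on imbalance seen in the data, the estimator is not fixed in advance, and the precision that baseline adjustment brings even when the groups are balanced is left to chance.

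A second pre-score also makes it worth naming the reference for percentage improvement. Take a hypothetical patient with NPQ 50 at screening, 45 at baseline and 34 later. Improvement is (50 - 34)/50 = 32% from screening, a success, but (45 - 34)/45 = 24% from baseline, a failure.

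**Working it through.** **1. The plan's own figure.** The article gives no precision figure for baseline adjustment. Its sample size reproduces: 95% against 85%, two-sided 0.05, power 0.80, with continuity correction, gives 160 per arm, so 320; 320/0.90 = 355.6, so 356. This is a comparison of two proportions with no covariate, and nothing below changes it.

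**2. Formula.** Let r be the correlation of each pre-score with the outcome (taken as equal for W-1 and W0) and rb the correlation between W-1 and W0. For a covariate-adjusted continuous score with unit variance:

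- residual variance with W0 only: 1 - r²
- residual variance with W-1 and W0: 1 - 2r²/(1 + rb)
- proportional reduction from adding W-1: r²(1 - rb) / [(1 + rb)(1 - r²)]

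**3. Inputs.** The article gives neither r nor rb for the NPQ, NDI or SF-36. Assumed ranges are rb 0.6-0.8 and r 0.4-0.6. The only reliability figure in the article is an intraclass correlation of 0.92 for the VAS (VAS section), used here as an alternative rb.

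**4. Results: reduction in residual variance from adding W-1 to W0.**

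| rb | r = 0.4 | r = 0.5 | r = 0.6 |
|---|---|---|---|
| 0.6 | 4.8% | 8.3% | 14.1% |
| 0.7 | 3.4% | 5.9% | 9.9% |
| 0.8 | 2.1% | 3.7% | 6.25% |
| 0.92 | 0.8% | 1.4% | 2.3% |

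The extremes of the assumed range, written out:

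- (rb 0.8, r 0.4): 0.840 falls to 1 - 0.32/1.8 = 0.822, a cut of 2.1%.
- (rb 0.6, r 0.6): 0.640 falls to 1 - 0.72/1.6 = 0.550, a cut of 14.1%.

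On the standard-error scale, 1 - √(1 - 0.021) = 1.1% and 1 - √(1 - 0.141) = 7.3%. Confidence intervals would be about 1% to 7% narrower.

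**5. Where the larger gain lies.** Against an unadjusted comparison at a single visit, W0 alone removes r² of the variance: 16%, 25% or 36% at r = 0.4, 0.5 or 0.6. Pre-specifying adjustment for W0 therefore matters more than adding W-1.

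**6. Effect of selection at entry.** The Inclusion criteria require a VAS above 3 at recruitment. In a simulation with an assumed cut 1 SD below the screening mean, the gain from W-1 fell from 6.3% to 5.2% (rb 0.8, r 0.6) and from 3.8% to 3.1% (rb 0.8, r 0.5).

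**7. The responder rate.** The formula does not apply to a binary outcome. A simulated illustration assumed NPQ means of 40 before and 14 after treatment, SD 12 for both, with values kept within the scale. Response was about 91-95%. Adding the screening score cut residual variance by 1.2-2.5% at rb 0.8 (r 0.5-0.7) and by 0.7% at rb 0.92 (r 0.6).

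**The case against.** The strongest reply is that nothing is shown to be lost. Three places in the article start the count at baseline, and baseline plus four later visits is a normal efficacy count. The section that says six may simply be counting the screening visit, where the VAS eligibility check is made. A reader might infer that a full second set of pre-randomisation scores is being thrown away. The article does not support that: no section says so, the Fig. 2 grid cannot be seen, and a fuller analysis plan may use the scores. This part of the objection stands.

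It is also fair that the choice of covariates is commonly left to the analysis plan, so omitting a covariate list is no fault. But the counts conflict within the article, and the article itself makes baseline adjustment conditional. Both are in the stated text.

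A reader might also turn the variance reduction into a firm saving, or into extra patients on 356. That fails too. The correlations are not in the article, the plan is a repeated measures analysis of variance rather than a covariate-adjusted one, and 356 rests on a responder rate.

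The worry over the reference score is small. The within-group paired tests in Statistical analyses start from baseline, and the Fig. 2 caption labels W0 as baseline, so W0 is the natural reading. The entry cut is on the VAS and would reach the NPQ only through their correlation.

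**Conclusion.** The point holds as a minor inconsistency with an optional improvement in efficiency attached. As written, any screening scores enter no described analysis, and adjustment for baseline depends on what the data show.

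The added value of W-1 beyond W0 for continuous scores is about 2-14% of residual variance under the assumed correlations. It is about 1-2% if the article's VAS reliability is taken as the correlation between the two pre-scores. Selection at entry lowers these figures somewhat. They require that the scale is in fact scored at screening and that the comparison is covariate-adjusted. They do not carry over to the NPQ responder rate or to the sample size. Leaving W-1 out of the model would not be an error.

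**What to change.** 1. Reconcile Outcome measurements with Interventions, the Fig. 1 caption and Statistical analyses by stating which scales are scored at W-1. If a scale is not scored then, its count is five.
2. In Primary outcome measurement, confirm W0 as the reference for percentage improvement in the NPQ.
3. For the continuous NPQ, VAS, NDI and SF-36 scores, replace the conditional covariance analysis with a pre-specified comparison of weeks 2, 4, 10 and 16, adjusted for the W0 score and, for any scale collected at screening, the W-1 score. W0 then enters as a covariate and not as a response. It cannot be both, so the repeated measures model should contain the four post-baseline visits only.

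The cost is a few sentences and no new data. The small downside is that patients missing one pre-score need a stated rule that the other is used alone.
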